**Fig. 1 Fig1:**
[figure not shown]
Study flow chart. The flow chart of enrolment, allocation, intervention and assessment. *Intervention Group has ten additional appointments for systematic orientation for a continuous global simulation at home and ten home visits

Sample size: the sample size was calculated on the basis of the results of many studies that assessed improvement of motor and mental development or cognitive or language acquisitions. All these studies obtained minimum scores 20% higher after early intervention. For a 5% level of significance and a statistical power of 80%, a sample size of 84 patients will be required to detect a 3-point between-group difference in development scores [20, 24–26]. The allocation of the subjects will be perfomed until the complete calculated sample size based on the number of premature infants who survive until hospital discharge. A number of 20% (number 16) will be added, considering possible loss or death during the follow-up. Total sample size will be 100 preterm infants.

Recruitment: strategies for achieving adequate participant enrolment to reach target sample size will be: to establish a link between the research team and mother and father of each of the subjects included, regardless of the group allocated since randomization. Weekly meetings are performed during NICU stay.

A telephone number is available twenty-four for all questions after discharge and during the follow up. This mobile phone stays each day with a researcher’s member on call to resolve doubts with clarity and security. A prior scheduling of home visits and office appointments is done continuously during the recruitment and assessment according the objectives.

Assignment of interventions: Monitoring the progress of this research is fundamental for assuring that all activities will be achieving stated milestones. The selection of adequate method for generating the randomization sequence is important for result measurements. We have used the research randomizer program available at www.randomizer.org [23].

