Simple randomization method for allocation: computer-generated random numbers for each 5 participants determines the allocation group. The trial is monitored during the process to have a balance in the number of subjects on each arm over time, eg, twins, triplets; they will be allocated for the same group. We have not stratification by gender, gestational age, or any other variable. In neonatal period, preterm infants will be sequentially randomized when they completed 48 h after birth. Randomization is performed by researchers that will not be responsible for any intervention, nor outcome measures of parental bond, motor and cognitive outcomes. The same researchers will register all neonatal data, discharge variables and the follow-up data, during the appointments (not blinded). During the NICU stay period, the nursing and the medical staff were informed that participating infants would receive an active intervention by the mothers depending on group allocation (not blinded). The data analysts, outcome assessors and the multidisciplinary team working in the institutional follow up clinic will be blinded.

The allocation of the subjects will be maintained until the complete sample size calculation. Both arms are routinely candidates for outpatient institutional follow-up clinic.

Data collection, management and analysis are being presented according checklist [23].

Data collection: Clinical morbidities and identification data were prospectively collected in duplicate during hospital stay until hospital discharge for the two independent researchers.

Both groups have all data obtained during regular appointments at the outpatient follow up clinic masked for allocation of patient groups. All variables will have double data entry in data record center storage.

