Growth velocity will be registered in the reference curves, using the two computers with an appropriate statistical program for nutritional assessment (ANTHRO). There are two nutritionists to perform the growth evaluations in the exact moments in each group (blinded to which group the child was previously allocated). In the Intervention Group there will be a Nutritionist that will make home visits with the team to reinforce breastfeeding practices. The research team is using a check list during the home visits to the Intervention Group; home visits should be done at least two more researchers.

Statistical methods: All analyses will be performed in the PASW Statistics® for Windows, Version 18.0 software environment (Chicago, IL: SPSS Inc. Released 2009). Qualitative variables will be expressed as absolute and relative frequencies. Pearson chi-square test will be employed to determine the association between categorical variables, with adjusted residuals in case of statistical significance.

Symmetrically distributed continuous variables will be described as means and standard deviations, while asymmetrical distributed categorical variables being described as medians and interquartile ranges. Fisher’s exact test for comparison of categorical variables and Student’s t or the Mann–Whitney tests for comparisons of symmetrically distributed quantitative variables and asymmetrically distributed variables, respectively will be used. Subgroup and any additional analyses will be performed to adjust for social status, maternal age and some preterm’s neonatal conditions associated with poor neurodevelopment outcome.

Monitoring: There are five researchers to monitor data without competing interest. All researchers are independent from sponsor. Data are continuously monitored during the study. The teaching activities and educational programs for the families will be the focus of our research group throughout the study and if some adverse events occur, will be reported. Previous published study showed that the intervention during NICU stay is safe; the 10 additional appointments and 10 home visits will check the intervention safety [23].

Table 2 summarizes the project framework regarding specific objectives, outcomes and period of activities.

**Table 2 Tab2:** Project Framework: specific objectives, outcomes and period of activities

Specific Objectives	Outcomes	Period acticvities
Objective 1:		

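### Siblings of a multiple birth are allocated together, but the sample size and the named tests treat every infant as independent

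*Protocol article*

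**What the plan says.** Three statements in the Methods of the protocol article have to be read together.

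- **Allocation** (Assignment of interventions, simple randomisation paragraph): for multiple births, "twins, triplets; they will be allocated for the same group". Multiples are not among the exclusions in the eligibility criteria.
- **Sample size** (Sample size paragraph): "For a 5% level of significance and a statistical power of 80%, a sample size of 84 patients will be required". The target is a gap of 3 points between the arms. A further 16 are added for possible loss or death, which gives 100 preterm infants. Both numbers count infants, and neither includes an allowance for siblings.
- **Analysis** (Statistical methods paragraph): "Pearson chi-square test will be employed to determine the association between categorical variables". Fisher's exact test is also named for categorical variables. For quantitative variables, Student's t and Mann-Whitney "tests for comparisons of symmetrically distributed quantitative variables and asymmetrically distributed variables, respectively will be used". Additional analyses adjust for social status, maternal age and some neonatal conditions. No family term, cluster-robust variance or rule of one infant per family is mentioned.

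**The concern.** All four named tests take their variance from the number of infants, as though each had been allocated separately. Infants from one multiple birth are not allocated separately, and there is good reason to expect their scores to be positively correlated. They share a mother, a pregnancy, a household income and a level of maternal education. In the intervention arm they also share how the intervention is delivered, because the same mother does the stimulation in the unit and the same parents do it at home with the same guidance and home visits.

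When correlated siblings always fall in the same arm, the true variance of the group difference is larger than the naive formula gives. P-values are then too small and confidence intervals too narrow for the Bayley III and AIMS comparisons, which are the primary outcome. The 84 infants also carry less information than 84 independent infants.

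A related ambiguity concerns the parent-level outcomes. Under Outcomes and in the participant timeline, stress and bonding at discharge are described as assessed for every included infant. The text does not say whether a mother of twins contributes one record or two.

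**Working it through.** **Inputs from the article.** Level 5%; power 80%; difference 3 points; 84 evaluable infants, taken as 42 per arm because the project framework table gives 50 per group out of 100. Sidedness is not stated, so two-sided is assumed.

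**Inputs assumed, because the article gives neither.** *p*, the share of analysed infants whose twin is also analysed: 10-40%. ICC, the correlation between siblings' scores: 0.3-0.9.

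**Step 1: the plan's own figure.** No SD is given, so 84 cannot be derived from the stated inputs. Solving backwards, SD = 3 × √(42/2) / (1.960 + 0.842) ≈ 4.91. An SD of 4.85 or 4.90 returns exactly 42 per arm. For what follows I take the plan at its word that 84 independent infants give 80% power. The expected test statistic is then 1.960 + 0.842 = 2.802, and the SD drops out of the later steps.

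**Step 2: design effect.** With twin pairs in the same arm, DE = 1 + *p* × ICC.
- Low end: 1 + 0.10 × 0.3 = 1.03
- Middle: 1 + 0.30 × 0.5 = 1.15
- High end: 1 + 0.40 × 0.9 = 1.36

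The naive standard error is too small by a factor √DE, about 1.01 to 1.17. Triplets would raise DE further.

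**Step 3: consequences.**
- True level of the planned tests: 2 × [1 − Φ(1.960/√DE)]
- Power of the planned tests, at that inflated level: Φ(0.842/√DE)
- Power of a valid clustered analysis at a true 5%: Φ(2.802/√DE − 1.960)
- Effective number of infants: 84/DE
- Evaluable infants needed for 80% power: 84 × DE, rounded up

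| *p* | ICC | DE | True level, planned tests | Power, planned tests | Power, valid analysis | Effective N | Infants needed |
|---|---|---|---|---|---|---|---|
| 10% | 0.3 | 1.03 | 5.35% | 79.7% | 78.8% | 81.6 | 87 |
| 20% | 0.5 | 1.10 | 6.17% | 78.9% | 76.2% | 76.4 | 93 |
| 30% | 0.5 | 1.15 | 6.76% | 78.4% | 74.3% | 73.0 | 97 |
| 40% | 0.7 | 1.28 | 8.32% | 77.2% | 69.7% | 65.6 | 108 |
| 40% | 0.9 | 1.36 | 9.28% | 76.5% | 67.1% | 61.8 | 115 |

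**Step 4: check by simulation.** Naive t tests with 42 infants per arm, *p* 20-40% and ICC 0.5-0.7 rejected a true null hypothesis in 6.2% to 8.1% of runs. The formula gives 6.2% to 8.3% over the same range.

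**Step 5: does the addition of 16 cover it?** No. It is reserved for loss or death, so 84 remains the planned evaluable number. In the middle case 97 evaluable infants are needed. Recruitment would then be 97/0.84, about 115, at the plan's implied loss (16/100 = 16%), or about 121 at a 20% loss (96.6/0.80).

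**The case against.** **The size rests on assumptions.** This is right. The article says nothing about how many multiples are expected, and a reader should not infer from it that they are common. At 10% and an ICC of 0.3 the true level is 5.35% and the valid power about 79%, which is of little practical weight. What matters for *p* is also the share of analysed infants with an analysed sibling. Pairs can be broken by early death, exclusion or loss to follow-up, so *p* is lower than the share born as multiples. If 16% were lost independently, for example, 20-40% would become about 17-34%.

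**The two losses belong to different analyses.** One might infer that the planned tests suffer both a 9% error rate and a fall to 67% power. They do not. The planned tests keep about 77-80% power because they run at an inflated level. The 67-79% applies to a valid clustered analysis.

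**Covariate adjustment may help.** Social status and maternal age are the same for siblings and could absorb part of the correlation. That applies only to the additional analyses. The named two-group tests are unadjusted, and the adjusted analyses have no family term for whatever correlation remains.

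**Parent outcomes are not stated to be counted twice.** Correct. The bonding questionnaire asks respondents about their own parents, so one form per respondent is the natural reading. The text leaves the unit open and states no rule of double counting.

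**An unseen analysis plan may deal with it.** Detail can be left to such a plan, but the article itself names the tests and the basis of the sample size. Both conflict with its own allocation rule, so a plan that handled clustering would have to replace this text.

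**Conclusion.** The concern holds in direction, while its size is unknown. Family-level allocation, an infant-level sample size and independence-based tests do not fit together. Given any positive sibling correlation, the planned tests do not hold the 5% level, and a valid analysis of 84 infants does not have 80% power.

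Over the assumed range (*p* 10-40%, ICC 0.3-0.9) the consequence runs from negligible to material. The middle case has a true level of 6.76% and 74% power for a valid analysis. The level figures do not depend on the missing SD. The power figures take the plan's claim of 80% at 84 independent infants as given.

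The documents do not support saying that the effect is certainly large, that the planned tests themselves fall to two-thirds power, or that parent outcomes will be duplicated.

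**What to change.** 1. State that the pregnancy or family is the unit of allocation.
2. Analyse infant outcomes with a method that accounts for family clustering. Options include a mixed model with a random intercept for family, or GEE or cluster-robust standard errors with a small-sample correction. Any of these would do, provided that one is chosen in advance.
3. Analyse parent-reported outcomes once per parent, and say so.
4. Restate the power for 84 evaluable infants with explicit assumptions for *p* and the ICC, multiplying the required number by 1 + *p* × ICC. The unit's own admission records could supply *p*.

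The article says that recruitment and data collection are still under way, so this can still be fixed in advance. It needs revised wording and a family identifier linking siblings in the data set, but no new visits or measurements. The price is slightly wider confidence intervals and a less favourable stated power, or a somewhat larger sample if 80% is to be kept.

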Interventions: Written informed consent was signed by the parents of all preterm infants that filled inclusion criteria in the study protocol. When they complete 48 h of life they are sequentially randomized. The intervention is planned to start on the 7th day of life according the randomization in two arms:

Conventional group (CG): Standard care, according to the routine care of the NICU: skin-to skin care by mother, kangaroo care, and breast feeding policy. After discharge they are referral for a traditional follow up clinic taking care of the demands according to their necessity; with motor, and cognition evaluations and interventions according to their needs.

Intervention group (IG): Skin-to skin care by mother, kangaroo care, breastfeeding policy plus massage therapy are made by the mothers until hospital discharge. After discharge, they receive standard follow up care plus orientation for a continuous global simulation at home. Early intervention will be according to developmental milestones, anticipating in one month evolutionary step acquisition of motor and / or cognitive expected for corrected age. Besides that, we have a total of 10 home visits promoting guidance and supervision sessions. After each appointment, there is one home visit. A number of ten orientations appointments and ten home visits must be completed for each subject included in the IG. A complete description for each group is detailed below:

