Follow up appointments, home visits, intervention during follow up program and all systematic orientation for early intervention have been done according to developmental milestones, anticipating in a month evolutionary step acquisition of motor and/or cognitive expected for corrected age. The theoretical neurodevelopmentalist referential of the main periods for the acquisition of developmental landmarks have been used [22].

During the sessions the patient should be well fed, have slept his nap and comfortable. Parents are learning to read your preterm’s behavior and respect their needs. We have distributed flyers with techniques and science-based activities to be applied systematically and sequentially at home. Parents have one flyer per appointment; a total of 10 flyers with orientations will be distributed for each subject of IG. Each patient will have a complete book of orientations in the end of the study.

In IG, during first six months corrected age, mother, father and / or corresponding caregivers have been received six flyers: simple guidelines to encourage large motor skills, fine and cognition and some toys.

From discharge up to three months corrected age: Sitting next to their children parents must place them on their stomach on the floor, being sure that their face, mouth, and nose is not covered, using a foam roller to position. Although tummy time is very important, preterm infants should also have time playing on their backs; so stimulation is also performed with the child in the position lying in bed or prone position and/or during bath; a number of three detailed guideline orientations is offered for each included family. Folders with detailed illustrations are offered to parents:

Gross and fine motor stimulation: Crossing arms and relaxation movements (play in the bath for 5 to 10 min, beating hands and feet in water, rubber animals). To make gymnastic movements with flexion and passive extension of the upper and lower limbs; in order to support themselves on the upper limbs in the prone position and to acquire the expected rolling ability.

Cognitive stimulation: Getting close and speak slowly, singing low. Use a mobile to look up, black and white gloves to put in the hands’ mother to play and the child turn your head 180 °C.

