Cognitive stimulation: parents are advised to read a book every day, and when they read these books, talk to child about these feelings. Get him to show how his face looks when he is mad, afraid, etc.… Talk repeatedly reinforcing each child’s achievement is very important all the time.

Material’s kit for the ninth and tenth appointments: Wooden poles with 60 cm in size each, two for each subject in the intervention group; four books with drawings of animals and objects and one case with 12 crayon colors for each subject.

All these activities must not use more than 15 min and they must seem games. Three times / week (alternating with gross and fine motor stimulation) and daily cognitive stimulation are recommended for IG plus conventional care according their needs. All parents will receive the same material kit for stimulation use that is sponsored by Bill and Melinda Gates Foundation. We have be done systematic orientations for cognitive stimulation, fine and gross motor, totaling 10 appointments and 10 home visits promoting guidance and supervision sessions. Systematic orientations will be delivered to parents in all medical appointments at follow up clinic. In the explanatory material for parents each description refers to an activity is a representative figure of the same proposal activity in order clearly to communicate for parents.

The aim of home visits is to evaluate the comprehension of the orientation and to be sure that the intervention has been done by families, a strategy to improve adherence to intervention protocol. During home visits pictures are taken, there is an explanation of the clinical relevance of the study and questions are promptly answered by the multidisciplinary team.

There is a multidisciplinary team involved in the whole study and we will have a critical view of the intervention impact (final evaluation) in both; conventional and intervention groups (Table 1).

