Other outcomes: Nutritional conditions during hospital stay and follow up program. Prevalence rates of exclusive breastfeeding and mixed feeding at 6 months corrected age will be recorded to measure maternal bond, in both groups. Anthropometric measures are plotted according to gender and corrected age using the WHO curves. Growth velocity has been registered in the reference curves, using two computers with an appropriate statistical program for nutritional assessment (ANTHRO). There is a nutritionist of the multidisciplinary group that makes home visits and other nutritionist to perform the growth evaluations in the exact moments in each group (blinded to which group the child was previously allocated).

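### Breastfeeding at 6 months corrected age cannot serve as a measure of maternal bond, because only the intervention arm gets home visits that reinforce breastfeeding

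*Protocol article*

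**What the plan says.** The Outcomes section has a primary outcome (AIMS and Bayley III), secondary outcomes, and a paragraph of other outcomes. That last paragraph gives breastfeeding a specific meaning: "Prevalence rates of exclusive breastfeeding and mixed feeding at 6 months corrected age will be recorded to measure maternal bond, in both groups".

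The growth paragraph just before Statistical methods describes a component given to one arm: "In the Intervention Group there will be a Nutritionist that will make home visits with the team to reinforce breastfeeding practices".

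Home visits belong to the intervention group (IG). In Methods, under Interventions: "A number of ten orientations appointments and ten home visits must be completed for each subject included in the IG". The visits are paired with the appointments: "After each appointment, there is one home visit".

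The same section lists routine care for the conventional group in the neonatal unit as "skin-to skin care by mother, kangaroo care, and breast feeding policy". The IG also receives the breastfeeding policy. After discharge both arms attend the follow-up clinic monthly until 6 months corrected age. Feeding advice is given there according to need, and the clinic team includes a nutritionist (Table 1).

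**The concern.** An indicator can stand in for a construct in a between-arm comparison only if the intervention does not also move the indicator by another route. Here breastfeeding is the indicator and maternal bond the construct, and one arm receives home support aimed at breastfeeding itself. Breastfeeding could rise in that arm with or without any change in bond.

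What is at stake is the interpretation of one result. If breastfeeding is more common in the intervention arm, the outcome as worded invites the conclusion that the programme strengthened the bond, and the data could not support that. Masked recording at the clinic does not help: it protects how feeding is ascertained, while the difficulty lies in the care that was given.

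**Working it through.** The protocol states no breastfeeding rate, and no sample size or hypothesis for this outcome, so there is no figure to reproduce. The check is a comparison of the text and a count of visits.

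1. **Support common to both arms.** Breastfeeding policy in the neonatal unit, and feeding advice at monthly clinic visits up to 6 months corrected age (Methods, descriptions of the two groups).

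2. **Support in the intervention arm only.** Nutritionist home visits to reinforce breastfeeding (growth paragraph before Statistical methods). The contrast is therefore routine support plus home reinforcement against routine support. It is not support against none.

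3. **Number of home visits.** The appointment blocks in Methods are three from discharge to 3 months corrected age, three from 3 to 6 months, two from 7 to 12 months and two from 13 to 18 months: 3 + 3 + 2 + 2 = 10. This agrees with the stated total of ten.

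4. **Visits around or before the measurement.** The first two blocks give 3 + 3 = 6 appointments. The flyer count agrees: "In IG, during first six months corrected age, mother, father and / or corresponding caregivers have been received six flyers", and "Parents have one flyer per appointment; a total of 10 flyers with orientations will be distributed for each subject of IG". With one visit after each appointment, up to about 6 of the 10 visits (6/10 = 60%) fall around or before 6 months corrected age. The conventional arm has 0 trial home visits.

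5. **Limits of that count.** Six is an upper limit on nutritionist contact. The text does not say that the nutritionist joins every visit. Each visit also follows its appointment, and the sixth appointment lies in the 3-to-6-month block, so the sixth visit could come after the feeding assessment.

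6. **Can the two explanations be separated?** Nothing in the article does so. No arm receives stimulation without the home feeding support, or the reverse, and no analysis is described that would distinguish them. With B for a change in bond and F for the direct effect of feeding support, the observed difference in breastfeeding reflects B, F or both. One between-arm contrast cannot apportion it.

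7. **Is another measure available?** The Outcomes section plans the Emotional Availability Scales (EAS) in both groups at the end of the study. They rate adult and child behaviour in the interaction directly. The Parental Bonding Instrument, as described there, asks respondents about their own parents' behaviour until age 16, so it is a weaker basis for claims about the present mother-infant relationship.

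**The case against.** The strongest reply is that little depends on this outcome. Breastfeeding sits below the primary and secondary tiers and does not appear in Table 2, which assigns bonding to the Parental Bonding Instrument. No conclusion announced in the Abstract or Discussion rests on breastfeeding as bond. This stands, and it is why the point is minor. It does not remove the stated purpose of the outcome, which is still to measure bond.

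A second reply is that controls are well supported on feeding too. That also stands. It narrows the contrast to the added home reinforcement but does not balance it.

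Three stronger readings are tempting, and the documents do not support them:

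- *A difference would show feeding support and not bonding.* Nothing in the text excludes a bonding effect, or says that home reinforcement of breastfeeding is unrelated to bond. What can be said is that the two are inseparable here.
- *The nutritionist is an undisclosed co-intervention.* The general statement of purpose does not mention feeding: "The aim of home visits is to evaluate the comprehension of the orientation and to be sure that the intervention has been done by families". However, the component is stated in the growth paragraph, and the other-outcomes paragraph also mentions a nutritionist who makes home visits. Where an article places such a detail is a matter of arrangement.
- *Growth and development comparisons are spoiled as well.* The Discussion plans to conclude about a continuous and global home intervention against standard care. That is a comparison of packages, and feeding support is part of the package. Growth is listed among nutritional outcomes, and no passage attributes it to stimulation alone.

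**Conclusion.** The point holds in a limited form. As worded, the plan would read as bond a behaviour that is directly promoted at home in one arm only, and it offers no way to separate the two explanations. The imbalance is up to about six home visits against none by around 6 months corrected age, with the nutritionist's share of those visits unstated. The effect on breastfeeding rates cannot be quantified from the document.

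The randomised comparison of breastfeeding remains valid as an effect of the whole package on feeding. The AIMS and Bayley comparison is not affected. The conclusion assumes that the nutritionist attends at least some visits before the 6-month assessment, which the stated purpose implies but no schedule confirms. Severity is minor.

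**What to change.** In the other-outcomes paragraph, delete the clause that makes the breastfeeding rates a measure of maternal bond. Report exclusive and mixed feeding at 6 months corrected age as feeding outcomes of the package, and say there that the package includes home reinforcement of breastfeeding. Base claims about the parent-infant relationship on the EAS.

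The cost is a change of wording: no visit, assessment or data item is added, because the EAS is already planned in both groups. The downside is that breastfeeding is lost as supporting evidence for bonding, and the EAS describes the relationship only at the end of the study, not at 6 months.
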